The loss of muscle mass, strength, and/or physical function is often referred to as sarcopenia, which is closely related to adverse clinical outcomes (15–17). Sarcopenia will have a major impact on the Asian aging population (26). The diagnosis of sarcopenia is also highly variable due to race, measurement methods, and living environments (27, 28). High-altitude hypoxia is considered to be able to facilitate sarcopenia and fat distribution (26, 29, 30). Chinese studies indicated that the incidences of sarcopenia in the high-altitude population (altitude>3500m and altitude at 2260m) were significantly higher than those in the plain population (26, 31). Specific cutoff values established according to altitudes for sarcopenia in the plateau populations seem more reasonable. However, very limited relevant studies are available. The assessment of muscle mass is a crucial element in diagnosing sarcopenia. Bioelectrical impedance analysis (BIA) or dual X-ray absorptiometry (DXA) were the most commonly used methods in the past. Nevertheless, the correlation of muscle mass with muscle strength, and more generically, with muscle function is low, and this discrepancy may be partially related to the presence of fatty infiltration (32, 33). The recent European Working Group on Sarcopenia in Older People recently replaced “low muscle mass” with “low muscle strength” as a primary determinant of sarcopenia (34) implying that muscle mass based on DXA and BIA may not be sufficient in the detection of sarcopenia and that methods with higher sensitivity in sarcopenia screening are warranted. Skeletal muscle area based on segmentation technology and muscle density measured by quantitative computed tomography (QCT) were considered to be more promising in the assessment of sarcopenia (35–37). However, the sarcopenia definition based on CT assessments of muscle size and density is lacking.

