As a province with an altitude fluctuation ranging from less than 100 meters to more than 3,000 meters, Yunnan province has a particular advantage in the study of the effects of altitude on osteoporosis and sarcopenia. This study is a multi-center cohort study in 12 regions where the altitude fluctuations range from 50 to 3500 meters. The primary aims of this study are listed as follows: Firstly, to compare the baseline prevalence of osteoporosis and sarcopenia in the over-50-year-old population at different altitudes and establish a provisional cut-off point based on QCT for the diagnosis of sarcopenia in adults according to altitude. Secondly, the bone and muscle characteristics of people at different altitudes are compared, such as bone density, muscle mass, muscle density, and biological indicators. Thirdly, follow up for 5 years and compare the incidence of adverse events (fall, osteoporosis fracture, death, etc) at different altitudes. The secondary study aims to explore the effect and mechanism of a high-altitude environment on the skeletal muscle system.

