### Recruitment strategy

The enrolment of potential subjects is assessed by investigators at each clinical center according to the inclusion and exclusion criteria. Each subject will sign an informed consent form before officially entering the study. The subjects of the SOY study are enrolled in 12 centers at different altitudes (**Figure 2**). The inclusion criteria are that participants should be aged over 50 years old and living at the research site for more than 10 years. Exclusion criteria were as follows: a. Inability to stand or walk independently; b. Deformity of the lumbar spine and hip joint; c. Tumors treated with radiotherapy or chemotherapy; d. Patients with metallic implants *in vivo*; e. Other serious or life-threatening diseases (e.g. severe stroke). Recruitment will start in August 2022 except for the main study center the First People’s Hospital of Yunnan Province in which recruitment started in April 2021. Baseline visits and follow-up details are shown in **Table 1**.

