**Figure 2 f2:**
[figure not shown]
Recruitment centers and specific altitude.

**Table 1 T1:** Items and procedures of the study at baseline and each follow-up.

	Baseline	1 year ± 30 days	2 years ± 30 days	3 years ± 30 days	4 years ± 30 days	5 years ± 30 days
Informed consent	X	–	–	–	–	–
Questionnaire survey	X	X	X	X	X	X
Muscle strength assessment (HGS)	X	X	X	X	X	X
Short physical performance battery (SPPB)	X	X	X	X	X	X
QCT scan	X	X	X	X	X	X
DXA scan	X^*^	X^*^	X^*^	X^*^	–	X^*^
Ultrasonic	X^*^	X^*^	X^*^	X^*^	–	X^*^
Blood collection	X^*^	X^*^	X^*^	X^*^	X^*^	X^*^

X, an item that will be collected.

X^*^, item that will be selectively carried out in viable centers.

-, item that will not be collected.

Ethical approval for the cohort study is obtained from the ethics committee of each study center [Main study center-The First People’s Hospital of Yunnan Province No. KHLL2021-KY056]. The study is conducted by ethical principles according to the Declaration of Helsinki. Radiation safety and protection measures are strictly implemented throughout the study. Informed consent is obtained from each participant at the nearest participating imaging center.

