**Figure 3 f3:**
[figure not shown]
Dual-energy X-ray absorptiometry (DXA) and computed tomography (CT) assessments. **(A)**: the whole body DXA scan for body composition analysis, mainly for the evaluation of muscle and fat mass. **(B)**: Areal BMD was calculated by the DXA scan of the lumbar spine and left hip. **(C)**~**(F)**: Muscle assessments with QCT including muscle density, muscle area, and intermuscular fat area. **(C)**: Measurement of trunk muscle at mid-L2 level; **(D)**: Measurement of cross-sectional area and mean computed tomography values of the gluteus maximus muscle at the level of the greater trochanter of the femur; **(E)**: Measurement of the gluteus medius and minimus muscle at the third sacral level; **(F)**: Measurement of the middle thigh muscle level. The muscle region is represented by the area highlighted in red. The area of intramuscular fat infiltration is obtained by subtracting the area of red ROI from the area of green ROI with the threshold segmentation method.

Notably, QCT is a required item for all research centers.

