### The diagnosis criteria of sarcopenia

According to the 2019 consensus update on sarcopenia diagnosis and treatment of the Asian working group for sarcopenia (AWGS 2019), the new diagnosis of sarcopenia was low muscle mass accompanied by low muscle strength or low physical performance. AWGS 2019 also defines persons with low muscle mass, low muscle strength, and low physical performance as having “severe sarcopenia” (30).

The specified cutoffs for each diagnostic component were as followed: low muscle strength was defined as handgrip strength < 28 kg for men and <18 kg for women; criteria for low physical performance were 6-m walk<1.0 m/s, short physical performance battery(SPPB) score ≤ 9, or 5-time chair stand test ≤ 12 seconds. Muscle mass assessment was retained the original cutoffs for height-adjusted: dual-energy X-ray absorptiometry<7.0 kg/m^2^ in men and <5.4 kg/m^2^ in women; and bioimpedance<7.0 kg/m^2^ in men and <5.7 kg/m^2^ in women.

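### The sarcopenia diagnosis needs a muscle-mass value that the schedule does not secure at every centre, so its prevalence cannot be compared across all 12 centres as written

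*Protocol article*

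**What the plan says.** All references are to the protocol article.

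- **Aim.** The end of the Introduction lists, as part of the first primary aim, "to compare the baseline prevalence of osteoporosis and sarcopenia in the over-50-year-old population at different altitudes". Under Recruitment strategy, "The subjects of the SOY study are enrolled in 12 centers at different altitudes".
- **Definition.** Under The diagnosis criteria of sarcopenia, "the new diagnosis of sarcopenia was low muscle mass accompanied by low muscle strength or low physical performance". The muscle-mass cut-offs are introduced by "Muscle mass assessment was retained the original cutoffs for height-adjusted: dual-energy X-ray absorptiometry" (7.0 kg/m² for men, 5.4 for women) and completed by "and bioimpedance<7.0 kg/m"² for men and 5.7 for women. No other muscle-mass method has a cut-off there.
- **Schedule.** Table 1 stars DXA at baseline and at years 1, 2, 3 and 5. The footnote defines a starred entry as an "item that will be selectively carried out in viable centers". Bioimpedance is not in Table 1, the Baseline visit section or the list of imaging assessments.
- **Required imaging.** Below Figure 3: "Notably, QCT is a required item for all research centers". The Introduction states that "the sarcopenia definition based on CT assessments of muscle size and density is lacking".
- **QCT cut-off.** The Statistical analysis section sets provisional QCT cut-offs at the 20th percentile of the population distribution, for variables used in screening.

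**The concern.** The diagnosis has a compulsory element that the compulsory measurements cannot supply. Handgrip and SPPB are unstarred at every visit, so strength and performance are available everywhere. Muscle mass, in a form to which a stated cut-off applies, is available only where DXA is done.

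The centres were chosen for their different altitudes, so a centre without DXA is a gap in the altitude range and not a random loss of participants. Adjusting for covariates cannot recover an altitude at which nobody has been diagnosed. The Discussion presents coverage of many altitudes as what this study adds over earlier two-altitude comparisons, so the gap falls on the study's main contribution.

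If the question is left open until data are in hand, the muscle-mass method would be chosen after the fact. If the method then differed between centres, a difference between methods could look like an effect of altitude.

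**Working it through.** **1. The passages side by side**

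| Element of the diagnosis | Measure with a stated cut-off | Required at every centre? |
|---|---|---|
| Low muscle mass (mandatory) | DXA | No, starred in Table 1 |
| | Bioimpedance | Not scheduled |
| | QCT | Required, but no cut-off in the criteria |
| Low strength | Handgrip | Yes |
| Low performance | SPPB or chair stand (also a 6-m walk, which is not scheduled) | Yes for SPPB |

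By contrast, osteoporosis is defined on QCT vertebral density and so can be assessed at all centres.

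**2. Does the 20th-percentile QCT cut-off fill the gap?** There are two ways to set it.

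- Within each altitude, as the aim of an altitude-specific cut-off suggests: about 20% fall below it at every altitude by construction, so it cannot show a difference in prevalence.
- On the pooled sample: proportions may differ by altitude, but this is a different definition from the one in the criteria section.

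Either way it is a provisional product of the study, not an element of the stated diagnosis.

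**3. The plan's own sample size.** Inputs from The estimation of sample size: fracture risk 6% against 6% × 1.5 = 9%, risk factor in 20% (ratio 1:4), two-sided 5%, power 80%, attrition 10%. Treated as two proportions, with pooled risk (0.09 + 4 × 0.06)/5 = 0.066:

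n(exposed) = [1.960 × √(1.25 × 0.066 × 0.934) + 0.842 × √(0.09 × 0.91 + 0.06 × 0.94/4)]² / 0.03² ≈ 720

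Total 720 × 5 = 3600, and 3600/0.90 = 4000, which is the stated figure. It counts every participant and allows 10% for attrition, with nothing for centres where sarcopenia cannot be diagnosed.

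**4. Size of the loss.** The number of DXA centres, k, is not given, so it is varied. Assumption: 12 equal centres, 4000/12 ≈ 333 each. Classifiable participants = 4000 × k/12.

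For scale, the last three columns give two-sided 5% power for a difference of 5 percentage points (the article's at least 5%, read as absolute) from three base prevalences: 5.5% and 25.7%, the ends of the article's sarcopenia range, and 16%, its overall osteoporosis figure, used as a middle value. This further assumes that DXA participants split into two equal altitude groups and that there is no clustering by centre.

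| DXA centres (k) | Classifiable | Base 5.5% | Base 16% | Base 25.7% |
|---|---|---|---|---|
| 3 | 1000 | 0.83 | 0.53 | 0.42 |
| 6 | 2000 | 0.99 | 0.82 | 0.70 |
| 8 | 2667 | 1.00 | 0.91 | 0.82 |
| 12 | 4000 | 1.00 | 0.98 | 0.94 |

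Worked case, k = 3, base 16% (500 per group, mean 18.5%): standard error under the null √(2 × 0.185 × 0.815/500) = 0.02456; under the alternative √[(0.16 × 0.84 + 0.21 × 0.79)/500] = 0.02451. Then z = (0.05 − 1.960 × 0.02456)/0.02451 = 0.076, and power = 0.53.

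**The case against.** **All 12 centres may turn out to have DXA.** The article gives no count, so this cannot be excluded, and the problem would then disappear for the baseline comparison. But the wording of the Table 1 footnote, the and/or between QCT and DXA in the Abstract and Baseline visit section, and the sentence singling out QCT as required all point the other way.

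**Some participants can be ruled out without DXA.** Someone with normal strength and normal performance does not meet the definition whatever their muscle mass. That stands, but at a centre without DXA it gives only a range for prevalence, from zero to the proportion with low strength or performance.

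**The comparison does not collapse.** A reader might infer that sarcopenia prevalence cannot be computed at all, or that the whole first primary aim fails. The documents do not support that. Prevalence can be computed at every DXA centre, osteoporosis is unaffected, and the aim of deriving a QCT cut-off is separate. With six DXA centres the illustrative power is still 0.70 to 0.99.

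**Confounding is not shown.** A reader might also infer that DXA availability is completely confounded with altitude. Availability goes with the centre. If DXA centres are spread over 50 to 3500 m, an altitude trend among them can be estimated; if they cluster at one end, it cannot. The text does not say which. Only the weaker statement holds: availability may be related to altitude.

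**Pooling of methods is not planned.** No section says that muscle-mass methods will be mixed across centres. This is a risk to close off, not an error in the plan.

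**Conclusion.** The contradiction is within the article and is not a detail left to an analysis plan: the definition, the schedule and the QCT requirement are all stated, and they do not fit together. At any centre without DXA nobody can be given the stated diagnosis, so the sarcopenia part of the first primary aim cannot be evaluated across all 12 centres.

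The size depends on the unstated number of DXA centres: about 1000, 2000 or 4000 classifiable participants for 3, 6 or 12, assuming equal centres. The power figures are illustrative and, because they ignore clustering, optimistic. The main loss is in the altitudes covered, and that depends on which centres have DXA as well as how many.

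It would be tempting to express the loss as residual degrees of freedom for a centre-level altitude slope. The article names one-way ANOVA and regression and no such slope, so that figure would not describe this plan.

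**What to change.** 1. State that sarcopenia prevalence under the published criteria, and its comparison by altitude, is restricted to named DXA centres. Give their altitude range and available sample size, and do not claim the result for all 12 altitudes.
2. Add an all-centre endpoint from the required handgrip and SPPB data, named low strength/low performance and not sarcopenia. First reconcile the performance criteria: the sarcopenia section uses a 6-m walk while the Baseline visit section schedules a 4-m gait speed, and the sarcopenia section labels a chair-stand time of 12 seconds or less as low performance, which would class the faster participants as low.
3. State that muscle-mass methods will not be pooled across centres in the main comparison. Any calibration of QCT muscle measures to DXA is exploratory. It assumes that the relation carries over to altitudes without DXA, which cannot be tested there, and a failure of that assumption could itself look like an altitude effect.

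The cost is wording and one added endpoint from data already scheduled, with no new scans. The downside is that the sarcopenia result covers fewer altitudes and participants, and the all-centre endpoint answers a related but different question. The change should be made before outcome data are examined.

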### Data management

All data will be transferred to the First People’s Hospital of Yunnan Province for analysis and quality control. The study data will be collected and managed in a database created using Epidata 3.1. Through this database, all questionnaire contents can be digitized to prepare for further classification, comparison, and statistical analysis, such as activity, diet habits, medication history, etc. All muscle function evaluations, imaging scans, and measurements were performed according to the unified standards of the study. All investigators taking care of data collection will be trained before the project begins.

### Statistical analysis

Baseline cross-sectional analysis between sarcopenia/osteoporosis and altitude will be conducted, including the prevalence, imaging parameters, SPPB, and blood sample indexes of skeletal muscle. The 5-year follow-up data will focus on comparing the rate of skeletal muscle degradation at different altitudes and the incidence of adverse events such as falls and fractures during the follow-up period. One-way ANOVA will be used to compare the research results between different altitudes. Multiple linear and logistic regression analyses were conducted to calculate the effects of various factors (e.g., altitude, age, and physical activity) on the skeletal muscle system in a high-altitude environment. Cox proportional hazards models were used to calculate the strength of BMD, muscle density, and muscle mass to predict the risk of major osteoporotic fractures. Provisional cutoff points based on QCT were defined for the variables used to screen for sarcopenia or osteoporosis using the 20th percentile of their population distributions.

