**Methods:**

This is a prospective, multicenter, cohort study, which will recruit a total of 4000 participants over 50 years from 12 research centers with different altitudes (50m~3500m). The study will consist of a baseline assessment and a 5-year follow-up. Participants will undergo assessments of demographic information, anthropomorphic measures, self-reported questionnaires, handgrip muscle strength assessment (HGS), short physical performance battery (SPPB), blood sample analysis, and imaging assessments (QCT and/or DXA, US) within a time frame of 3 days after inclusion. A 5-year follow-up will be conducted to evaluate the changes in muscle size, density, and fat infiltration in different muscles; the muscle function impairment; the decrease in BMD; and the osteoporotic fracture incidence. Statistical analyses will be used to compare the research results between different altitudes. Multiple linear, logistic regression and classification tree analyses will be conducted to calculate the effects of various factors (e.g., altitude, age, and physical activity) on the skeletal muscle system in a high-altitude environment. Finally, a provisional cut-off point for the diagnosis of sarcopenia in adults at different altitudes will be calculated.

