### Strengths and limitations of this study

The strengths of this study were listed as follows: Firstly, this is the first multicenter cohort study about bone and muscle characteristics of adults at different altitudes and would provide valuable reference data for adults aged over 50 years in plateau areas.

Secondly, the 5-year follow-up design provides longitudinal comparative data. Detailed changes and potential relationships in bone mass and muscle characteristics of older adults in high-altitude hypoxia environments can be dynamically recorded for further analysis. QCT and/or DXA measurements can provide more accurate assessment means of osteoporosis and sarcopenia diagnosis.

By the way, the limitations of this study are deserving of attention. Firstly, there is potential for high dropout rates of older adult participants due to physical decline or death. Secondly, external validation is lacking in this study.

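### The primary aim of comparing 5-year falls, fractures and deaths across altitudes has no stated method that handles follow-up time and censoring: ANOVA is the named comparison, and the Cox model omits altitude

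*Protocol article*

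**What the plan says.** The third primary aim, at the end of the Introduction, is to "follow up for 5 years and compare the incidence of adverse events (fall, osteoporosis fracture, death, etc) at different altitudes".

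The Statistical analysis section describes the follow-up analysis as "comparing the rate of skeletal muscle degradation at different altitudes and the incidence of adverse events such as falls and fractures". The next sentence reads: "One-way ANOVA will be used to compare the research results between different altitudes". It is not restricted to the baseline visit or to continuous outcomes.

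Two other methods follow in the same section:

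- **Regression:** "Multiple linear and logistic regression analyses were conducted to calculate the effects of various factors (e.g., altitude, age, and physical activity". The outcome is the skeletal muscle system. The abstract repeats this and adds classification trees.
- **Cox:** "Cox proportional hazards models were used to calculate the strength of BMD, muscle density, and muscle mass to predict the risk" of major osteoporotic fractures. Altitude is not listed.

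The sample size section justifies 4000 participants partly by a survival analysis of fracture over 5 years and allows about 10% attrition. Table 1 schedules the questionnaire, grip strength, SPPB and QCT at baseline and at each of years 1 to 5. The limitations section warns that "there is potential for high dropout rates of older adult participants due to physical decline or death".

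**The concern.** Falls, fractures and deaths over 5 years are events observed over unequal follow-up. One-way ANOVA on whether an event was seen treats a person lost in year 1 without a fracture the same as one followed for 5 years without a fracture. It does not adjust for age or sex, and it gives no role to death, which prevents a later fracture from being observed. If dropout differs between centres, crude incidence differs between altitudes even when the underlying risk does not.

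The annual muscle, bone and function measures raise a related problem. They are repeated within a person, and no stated method models that repetition against altitude.

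At stake is the altitude contrast for a primary aim. The article has data suited to a better analysis and sizes the cohort for one, yet the comparison it names does not use follow-up time.

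**Working it through.** **1. The plan's own figure.** Inputs from the sample size section: background 5-year fracture risk 6%, raised by 50% to 9%; risk factor present in 20%; two-sided 5%; power 80%; attrition 10%.

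- *Two proportions, 4:1 allocation.* Let k = 0.25 and p̄ = (0.06 + 0.25 × 0.09)/1.25 = 0.066. Then n(unexposed) = [1.96√(p̄(1−p̄)(1+1/k)) + 0.842√(0.06×0.94 + 0.09×0.91/k)]² / 0.03² = 2879. The total is 2879 × 1.25 = 3599, and 3599/0.9 = 3999.
- *Freedman log-rank, unequal allocation.* Events = 7.849 × (1 + 0.25×1.5)² / (0.25 × 0.5²) = 237.4. The overall risk is 0.8×0.06 + 0.2×0.09 = 0.066, so N = 237.4/0.066 = 3597, and 3597/0.9 = 3997.

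Both reproduce 4000, so the sample size is not in dispute here. Its stated basis is a survival analysis.

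**2. Stated methods against what the follow-up aims need.**

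| Stated method | Includes altitude? | Uses follow-up time and censoring? | Models repeated visits? |
|---|---|---|---|
| One-way ANOVA | Yes | No | No (at best through a per-person summary) |
| Linear and logistic regression | Yes, with age | No | Not as stated |
| Classification trees (abstract) | Yes | Not as stated | Not as stated |
| Cox model | Not listed | Yes | Not applicable |

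No row says yes to both of the first two questions, and none models repeated visits by altitude.

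**3. How unequal dropout distorts crude incidence.** Assume constant event hazard λ = −ln(1−risk)/5 and dropout hazard c = −ln(1−d)/5, where d is 5-year dropout. The expected observed proportion with an event is λ/(λ+c) × [1 − (1−risk)(1−d)].

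- Risk 6% (λ = 0.01238). At d = 5%, c = 0.01026: 0.01238/0.02263 × 0.107 = 5.85%. At d = 15%, c = 0.03250: 0.01238/0.04488 × 0.201 = 5.54%. At d = 40%, c = 0.10217: 0.01238/0.11454 × 0.436 = 4.71%.
- Risk 30% (assumed, λ = 0.07133). At d = 5%: 0.07133/0.08159 × 0.335 = 29.3%. At d = 40%: 0.07133/0.17350 × 0.580 = 23.8%.

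The true risk is identical throughout; only dropout moves the figure.

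**4. Effect on the test.** The simulation used 12 centres of 333, equal hazards everywhere, exponential dropout rising linearly across centres, and 600 runs per scenario. It compared one-way ANOVA on the event indicator with a 12-sample log-rank test, both at nominal 5%.

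| Dropout across centres | Risk 6%: ANOVA / log-rank | Risk 30% (assumed): ANOVA / log-rank |
|---|---|---|
| 10% everywhere | 4.0% / 4.0% | 4.7% / 5.0% |
| 5-15% | 5.5% / 4.8% | 8.2% / 5.3% |
| 5-40% | 7.3% / 3.7% | 27% / 4.8% |
| 10-60% | 12.7% / 5.5% | 76% / 4.2% |

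The Monte Carlo standard error at a true 5% is √(0.05×0.95/600) = 0.9 percentage points. So 5.5% cannot be told from 5%, and 7.3% is a modest excess. The dropout ranges are assumptions; the article gives only about 10% overall and a warning that it could be high.

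**The case against.** The strongest reply is that ANOVA does not stand alone. The abstract and the Statistical analysis section both name linear and logistic regression with altitude and age as factors. That is right, and it answers much of the confounding worry for muscle and bone outcomes and for baseline prevalence. A reader might infer that ANOVA is the only stated test across altitudes; the text does not support that. The regressions are not stated for falls, fractures or deaths, however, and logistic regression also ignores censoring.

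A reader might also infer that ANOVA commits the study to a first-to-last change in completers. It does not. The section speaks of a rate, and a slope fitted to each person's available visits can be compared by ANOVA, including people who drop out after two or more visits. No completers-only rule is stated. What remains is that such an analysis, if intended, is not described, and the test itself is unadjusted.

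Third, a survival analysis and Cox models are both mentioned, so time-to-event methods are planned, and a condensed article may leave model detail to a fuller document. That stands for detail such as covariate lists or missing-data handling, whose absence is no fault here. It does not cover a comparison the article itself fixes, nor a Cox sentence that lists predictors without altitude.

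Finally, on the article's own figures the error inflation is negligible, as the 5-15% row at 6% risk shows. That also stands and limits the size of the point.

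**Conclusion.** The point holds in limited form. For between-altitude results the article names one-way ANOVA without restriction. Its regressions include altitude but are not described as longitudinal or time-to-event, and its Cox model does not list altitude. The third primary aim therefore lacks a stated method that accounts for follow-up time, censoring or death as a competing event.

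The numerical harm is conditional. It is nil with equal dropout and negligible for fracture at 6% risk with 5-15% dropout. It becomes material only if dropout varies strongly with altitude, and more so for commoner events: about 7% at 6% risk and 27% at 30% risk, for dropout of 5-40%. Those ranges and the 30% risk are assumed. The simulation also assumes constant hazards and dropout unrelated to the individual's risk within a centre, and it did not model death as a competing event. It should not be read as showing that the planned results will be biased.

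**What to change.** Amend the Statistical analysis section:

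- Limit one-way ANOVA to descriptive baseline comparison of continuous measures.
- **Fracture and death:** Cox models with altitude as the exposure, continuous or in bands, adjusted for age and sex, with death treated as a competing event for fracture. The existing Cox analysis of BMD and muscle as predictors can stay as a separate question.
- **Falls:** a person-time count model (Poisson or negative binomial), since falls recur.
- **Annual muscle, BMD and function measures:** a linear mixed model with an altitude × time term on all available visits, adjusted for age and sex.
- Report dropout and its timing by altitude, so that readers can judge which row of the table above applies.

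The cost is analysis wording and code. The annual visits and the fall and fracture histories are already planned, and death is already a named outcome. The sample size need not change on this account.

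### Altitude is essentially a property of 12 centres, but the named altitude analyses treat participants as independent, so centre differences unrelated to altitude can be reported as altitude effects

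*Protocol article*

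**What the plan says.** On the design, the Recruitment strategy section says "The subjects of the SOY study are enrolled in 12 centers at different altitudes". Eligibility requires "living at the research site for more than 10 years", and Figure 2 is captioned "Recruitment centers and specific altitude". The same section gives August 2022 as the start of recruitment, "except for the main study center", which began in April 2021.

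On the analysis, the Statistical analysis section says "One-way ANOVA will be used to compare the research results between different altitudes". It continues: "Multiple linear and logistic regression analyses were conducted to calculate the effects of various factors", with altitude, age and physical activity as the examples. Cox models are named separately, to predict fracture from bone and muscle measures. The section mentions no centre term, random effect, generalised estimating equation or cluster-robust error.

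The sample size section claims that 4000 participants suffice to detect a prevalence difference of at least 5% between the highest and lowest altitude. It mentions no design effect. The limitations name dropout and the lack of external validation, but not this issue.

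**The concern.** Comparing altitudes is at the core of the primary aims in the Introduction. If everyone at a centre shares roughly one altitude, then anything else that shifts a whole centre's mean is indistinguishable, within that centre, from an altitude effect. One-way ANOVA has a single factor. If each centre is its own altitude level, the test asks only whether centres differ. If centres are grouped into bands, or altitude enters as a linear term, centre variation still feeds the estimate while the standard error is computed from individuals. In each case the p-value for altitude answers a different question from the one asked, and small centre shifts can be published as effects of hypoxia.

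One centre-level difference is documented: the main centre started 16 months before the others (April 2021 to August 2022).

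**Working it through.** **1. Does the plan's own figure contain an allowance for clustering?** Inputs from the sample size section: background fracture risk 6%, raised by 50% to 9%; risk factor present in 20% (ratio 0.25 exposed to unexposed); two-sided 5%; power 80%; attrition 10%. Using the two-proportion formula with pooled variance under the null:

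- pooled risk = (0.06 + 0.25 × 0.09)/1.25 = 0.066
- n unexposed = [1.960 × √(0.066 × 0.934 × 5) + 0.842 × √(0.06 × 0.94 + 0.09 × 0.91/0.25)]² / 0.03² = 2879
- total = 2879 × 1.25 = 3599; with attrition, 3599/0.90 = 3999

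The stated 4000 is therefore reproduced by a formula for independent subjects. Other formulas give other totals (4228 with continuity correction; 5034 from a hazard-ratio formula), so the match shows consistency and does not prove which method was used. It leaves no visible room for a design effect.

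**2. Inputs for the error rate.** From the documents: 12 centres, 4000 participants, altitudes 50 to 3500 m, alpha 0.05. Assumed: equal centres (m = 4000/12 = 333), equally spaced altitudes, a normal outcome with total variance 1, no true altitude effect, and an ICC of 0.001 to 0.02. An ICC of 0.01 means a between-centre standard deviation of √0.01 = 0.1 of the outcome's standard deviation.

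**3. Formulas.**

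- Design effect: D = 1 + (m − 1) × ICC
- Understatement of the standard error: √D
- Effective sample size for altitude: 4000/D
- Linear altitude term: error = P(|Z| > 1.96/√D)
- Three bands of four centres: error ≈ 0.05^(1/D), from the 2-df chi-square
- 12-level ANOVA: error = P(F > 1.79 × (1 − ICC)/D), where F has 11 and about 3988 df and 1.79 is the 5% critical value

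Worked at ICC 0.01: D = 1 + 332.3 × 0.01 = 4.32; √D = 2.1; effective N = 4000/4.32 = 925; linear term P(|Z| > 0.943) = 35%; three bands 0.05^(1/4.32) = 50%; 12 levels P(F > 0.41) = 95%.

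**4. Simulation**, 40,000 runs per ICC, nominal 5%, which agrees with the formulas to within about one point:

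| ICC | D | SE understated by | Effective N | 12-level ANOVA | Three bands | Linear term | Centre-level slope, 10 df |
|---|---|---|---|---|---|---|---|
| 0 | 1 | 1.0 | 4000 | 5% | 5% | 5% | 5% |
| 0.001 | 1.33 | 1.2 | 3002 | 19% | 10% | 9% | 5% |
| 0.005 | 2.66 | 1.6 | 1503 | 77% | 33% | 23% | 5% |
| 0.01 | 4.32 | 2.1 | 925 | 95% | 50% | 34% | 5% |
| 0.02 | 7.65 | 2.8 | 523 | 99.5% | 68% | 48% | 5% |

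**5. The highest-versus-lowest claim.** The contrast is taken as 16% versus 21%, using the stated overall prevalence of osteoporosis. If it means one centre against one centre, 333 against 333 has about 38% power even with independent subjects. If it means one band of four centres against another (1333 each), power under independence is about 91%. At an assumed ICC of 0.01, though, each band is worth 1333/4.32 = 309 people, and power falls to between 35% (300 per group) and 38% (333 per group), before any loss from small-sample degrees of freedom.

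**The case against.** The strongest reply is that this is a condensed article, and centre terms in the regressions may stand in a full plan that is not shown. That holds in part for the regressions. It does not hold for one-way ANOVA, which the article names as the altitude comparison and which cannot contain a centre term.

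Second, altitude coding is not stated and Figure 2 is not visible. The Introduction grades altitude in bands, so 12 levels is the worst case. This stands, and it is why all three codings are shown; none holds 5% once the ICC is above zero.

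Third, residents of one site may live at somewhat different altitudes. That is possible, but the design identifies altitude by centre, and modest variation within a centre would not change the picture much.

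Fourth, phantom cross-calibration, unified standards and training limit measurement differences. They do, but they do not touch differences in population, recruitment or calendar time.

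A reader might also infer more than the documents support:

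- **That centres differ in scanners, assessors, ethnicity, diet or recruitment source.** Only the start date is documented. Ethnicity and diet are recorded, but nothing says they vary by centre.
- **That ANOVA leaves age and sex unadjusted and is misapplied to binary outcomes.** The planned regressions largely answer this: age is listed, the covariate list is open, sex is collected, and logistic regression suits binary results.
- **That the sex mix alone could produce the 5-point difference.** This needs stacked assumptions about the share of women and the prevalence in men, neither of which is given.
- **That the Cox models need a centre frailty for the same reason.** They predict fracture from individual-level measures, so they lie outside this defect.

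**Conclusion.** The concern holds. The named altitude analyses ignore the level at which altitude varies, so their p-values and confidence intervals for a primary aim are not valid as written. The size depends on the ICC, which the documents do not give, and on how altitude is coded. For an assumed ICC of 0.001 to 0.02, the false-positive rate is 19% to 99.5% (12 levels), 10% to 68% (three bands) or 9% to 48% (linear term), and the standard error is understated about 1.2- to 2.8-fold.

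It would go too far to say that every centre difference will be declared an altitude effect, or that a false altitude finding is almost certain. That is close to true only for the 12-level ANOVA at ICC 0.01 or above. Nor are standard errors generally several times too small: at ICC 0.005 to 0.01 the factor is 1.6 to 2.1.

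**What to change.** - Make the primary altitude comparison a mixed model, linear for continuous and logistic for binary outcomes, with a random intercept for centre. Enter altitude as continuous or in prespecified bands of several centres each. A fixed effect for every centre is not an option, because it would absorb altitude.
- Use small-sample degrees of freedom: 12 − 2 = 10 for a slope, 12 − 3 = 9 for three bands. A centre-level analysis on the same degrees of freedom is an acceptable equivalent.
- Adjust for age, sex and ethnicity, all of which the baseline visit already collects.
- Keep one-way ANOVA and centre means as description only.
- State as a limitation that 12 centres cannot fully separate altitude from other centre-level differences, including the main centre's earlier start. A random intercept corrects the error rate; it does not remove confounding between centres.
- Restate the highest-versus-lowest altitude claim in the sample size section with an assumed ICC, and say which centres or bands are contrasted.

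No new data are needed. The cost is revised analysis wording and a new power calculation, wider confidence intervals for altitude, and a less favourable power statement than the present one.
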